### Sample size

A sample size of 1,410 people (705 in each group, with a loss to follow-up rate of 20% and at least 25% Māori in the sample) is required for this trial. This number will provide 90% power at p = 0.05 to detect a difference in point prevalence abstinence of 7.5% at six months. In addition, this sample size will allow the consistency of effects for pre-specified subgroups to be assessed. It is expected to take 18 months to recruit the required sample size, based on a previous cessation trial run through the New Zealand Quitline [10].

### Withdrawal criteria

If, at any time after randomisation, significant intolerance to the study treatment is suspected, the treatment (or control) can be withdrawn. Should participants require discontinuation of study treatment for any reason (see below), or if they elect to cease taking treatment, follow-up calls and data collection will continue as scheduled as if they were continuing with the randomised treatment. Participants may have the study treatment withdrawn if one or more of the following occurs:

• The participant makes a voluntary decision to withdraw from follow-up, or from the treatment.

• The participant has any serious clinical adverse event, intercurrent illness, or other medical condition that indicates to the principal investigator that continued treatment with the study treatment is not in the best interest of the participant. The study treatment will be withdrawn if the participant develops any life threatening or seriously disabling illness or is admitted to hospital.

• The participant becomes pregnant during the course of the trial. Such participants will be asked to discuss on-going NRT use with their general practitioner or lead maternity caregiver.

• The investigator feels that it is in the best interests of the participant.

• The study is terminated.

If the participant discontinues treatment due to a serious adverse event, the participant will be followed until the event resolves or there is a return to a clinically acceptable medical status. Participant deaths or serious adverse events, which occur within 30 days of discontinuation, will be reported to the project co-ordinator.

### Data management

The design and management of all databases associated with this trial will be undertaken by the data management and information technology groups at the Clinical Trials Research Unit. Data will be stored in the Unit's Oracle database and linked to the electronic Case Record Form (CRF) data where applicable. Validation rules for each CRF will be specified by the project co-ordinator, in association with the senior data manager. These rules will include range checks so that inaccuracies in data collection can be identified early. A query will be raised as soon as any values are entered that are outside the allowed range or if data are missing. The research assistants at Quitline will amend the form as soon as a query is raised.

### Data monitoring

An independent person will monitor the trial conduct. This monitor will audit Quitline and the Clinical Trials Research Unit during the trial to ensure that the study protocol is being adhered to. At Quitline the monitor will audit every randomised participant's records to ensure their existence, that they meet the inclusion criteria and have provided informed consent, and that the treatment is being distributed within the limits of the protocol. The monitor will review the study documentation and records held by Quitline to ensure that documentation is up-to-date and record keeping meets the requirements specified in the protocol and complies with regulatory requirements. The monitor will visit Quitline early on during the study (after ten participants have been randomised), at study close-out and twice during the course of the trial. The monitoring task for the trial is unlikely to be onerous as the majority of data for this trial will be collected electronically, with range and logic checks built into the programme used. In the rare event that the computer programme is not accessible (e.g. power cut, system down), hard copies of the CRF's will be completed by the research assistants at Quitline, with the data entered onto the Unit's computer database at a later stage. Hard copies of the CRF's will be checked for consistency by the monitor and checked against the electronic copy. The monitor will audit the Unit every three months to see that the product supply records are in order and that there are sufficient supplies remaining, that the nicotine-free cigarettes are being stored appropriately and that the handling of unused nicotine-free cigarettes complies with study procedures. A Data Safety and Monitoring Committee has not been established for this trial as the trial does not meet two or more of the criteria stipulated by Ellenburg el al (2002), for setting up such a committee [11].

### Data analyses

This trial has been designed with the assistance of a senior statistician at the Clinical Trials Research Unit, who will continue to advise and assist with analyses of the trial data.

#### Treatment effects

Analyses will be undertaken on an intention-to-treat basis, according to a pre-specified statistical analysis plan using SAS version 9.1.3. A per-protocol analysis will also be performed in order to check the robustness of the results. No interim analysis will be undertaken. Chi-squared analyses will be used to compare the proportion quit by treatment group, and incidence rates, relative risks, risk differences, 95% confidence intervals and two-sided p-values will be calculated. Logistic regression analyses will be utilized to adjust for important prognostic factors. Continuous outcome data will be analysed using multiple linear regression modelling. Both the number of cigarettes per day and withdrawal symptoms over time will be compared using analysis of covariance. Pre-specified subgroup analyses using tests for heterogeneity will be undertaken for ethnicity (Māori, non-Māori), age (< 40 years, ≥ 40 years), sex and socioeconomic status (dichotomised as those who left school below Year 12 or with no school qualification, and those who completed Year 12 and above). Analyses will also be undertaken to examine time-to-first-lapse using Kaplan-Meier analysis and self-reported seven-day point prevalence of smoking abstinence at six months in those with complete smoking status data.

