### Randomisation: allocation concealment and sequence generation

All potential participants will be assigned a unique registration number allocated by a central computer following details submitted on a web-based form. This number will be used to identify each randomised participant who has consented to take part. Participants will be randomised by computer, with stratified minimisation by sex, ethnicity (Māori, non-Māori), and level of nicotine dependence (> 5 points, ≤ 5 points on the Fagerström Test of Nicotine Dependence (FTND) Questionnaire [6]), to ensure a balance in these key prognostic indicators between the intervention and control group.

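### The six-month abstinence comparison could be adjusted for the three minimisation factors at no cost; the unadjusted chi-squared test is valid but gives up a little precision

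*Protocol article*

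**What the plan says.** Under *Randomisation: allocation concealment and sequence generation* the protocol article states: "Participants will be randomised by computer, with stratified minimisation by sex, ethnicity (Māori, non-Māori), and level of nicotine dependence". Ethnicity is Māori or non-Māori, and dependence is split at 5 points on the FTND. The stated purpose is "to ensure a balance in these key prognostic indicators between the intervention and control group".

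Under *Treatment effects* it states: "Chi-squared analyses will be used to compare the proportion quit by treatment group". The same sentence lists the quantities to be reported, including relative risks and risk differences, and ends: "95% confidence intervals and two-sided p-values will be calculated". The next sentence reads: "Logistic regression analyses will be utilized to adjust for important prognostic factors". It does not name those factors, mention the minimisation factors, or say how the logistic result stands in relation to the chi-squared result. The section refers to a pre-specified analysis plan, which is not available here.

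Under *Baseline assessments*, sex, ethnicity and FTND level are all collected before randomisation.

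**The concern.** Minimisation keeps the arms alike on the chosen factors. If those factors predict quitting, chance imbalance on them no longer contributes to the difference between arms, but the usual chi-squared variance still allows for it. The standard error is then somewhat too large, the interval somewhat too wide and the test somewhat cautious. Adjusting for the factors used in allocation brings the analysis into line with the design.

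The planned logistic model does not fully meet the point. As written, its covariates need not be the three minimisation factors. A standard logistic model also yields an odds ratio, so the relative risk and risk difference that the article promises remain unadjusted. What is at stake is a small amount of precision in the trial's main result.

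**Working it through.** **Inputs from the article.** The total is 1,410, or 705 per arm, allowing for 20% loss and with Māori making up a quarter or more. On power, the *Sample size* section says: "This number will provide 90% power at p = 0.05 to detect a difference in point prevalence abstinence of 7.5% at six months". P-values are two-sided. Participants lost to follow-up are counted as smokers.

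**Assumptions, not in the article.** Control quit rate; factor prevalences of 50%, 25% and 50%; odds ratios of the factors for quitting; minimisation with a biased coin of probability 0.8.

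**Step 1: the planned sample size.** It cannot be reproduced from the stated inputs, because no control rate is given, so a rate was back-solved. With p1 = 0.15, p2 = 0.225 and mean p = 0.1875:

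n per arm = [1.96·√(2·0.1875·0.8125) + 1.2816·√(0.15·0.85 + 0.225·0.775)]² / 0.075² = 568 (rounded up).

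Dividing by (1 − 0.20) gives 710 per arm, or 1,420 in total, against 1,410. With 705 × 0.8 = 564 per arm, power is 89.8%. A control rate near 15% therefore fits the plan; 10% would need 1,104 and 20% would need 1,688.

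**Step 2: where precision is lost.** Let w be the share of participants in each stratum and p_s its quit rate. Then

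p(1 − p) = Σ w·p_s(1 − p_s) + Σ w·(p_s − p)².

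The chi-squared test uses the whole left side. When the arms are balanced on the strata, only the first term on the right drives the difference between arms. The second term is the excess. It is zero if the factors do not predict quitting and grows with their strength.

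**Step 3: how much.** Minimised trials were simulated, 4,000 per setting, comparing the chi-squared test with logistic regression adjusted for the three factors. The factor odds ratios were: modest 1.2, 1/1.3, 1/1.6; strong 1.5, 1/2, 1/2.5; very strong 2, 1/3, 1/4. Each cell shows chi-squared / adjusted.

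| Setting | Factors | Type I error (%) | Power (%) | Gain (points) |
|---|---|---|---|---|
| 15% v 22.5%, 1,128 followed up | modest | 5.2 / 5.2 | 89.8 / 89.9 | 0.15 |
| | strong | 5.1 / 5.4 | 90.0 / 90.7 | 0.7 |
| | very strong | 4.0 / 4.8 | 91.0 / 92.7 | 1.65 |
| 12% v 18%, all 1,410 | modest | 4.7 / 4.7 | 88.6 / 88.8 | 0.2 |
| | strong | 4.6 / 4.8 | 89.1 / 89.6 | 0.5 |
| | very strong | 4.2 / 4.9 | 90.0 / 91.5 | 1.5 |

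The second setting is the first with 20% lost and counted as smokers (0.8 × 15% = 12%; 0.8 × 22.5% = 18%). Monte Carlo standard errors are about 0.35 points for type I error and 0.5 for power. Both tests are applied to the same simulated trials, so the gains are more precise than that.

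A separate simulation (12% v 18%, 705 per arm, balance within the 8 strata, odds ratios 0.4 to 0.8) compared chi-squared with a stratified analysis. Power was 0.891/0.893, 0.873/0.879 and 0.897/0.903. Null rejection was 0.050/0.050, 0.045/0.047 and 0.049/0.054.

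A setting with higher quit rates (18% v 24%, 1,410 analysed, 3,000 runs) gave larger gains: 0.3, 1.3 and 3.4 points for modest, strong and very strong factors. Power there is only about 79%. It implies 0.18/0.8 = 22.5% quitting among controls followed up, and even a 22% rate would need 892 per arm rather than 705. That setting does not fit the planned sample size.

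**Step 4: in participants.** At 15% v 22.5%, raising 564 per arm to 564/0.98 (about 12 more) lifts power from 89.8% to 90.4%, and 564/0.95 (about 30 more) lifts it to 91.3%. So the gain with strong factors is worth roughly 2% to 3% of the sample, and the gain with very strong factors somewhat more than 5%.

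**The case against.** The case against is substantial, and most of it stands. Adjustment is already planned, in the sentence after the chi-squared test. The natural reading is that the key prognostic indicators used for minimisation are among the important prognostic factors to be adjusted for. The covariate list and the order of the two analyses are matters that an article may leave to the analysis plan. The unadjusted test estimates the marginal difference in proportions validly, and that is the quantity on which the sample size rests. With modest factors the loss is barely measurable.

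Two stronger readings are tempting, and the documents support neither. The first is that ignoring minimisation makes the p-value wrong in a harmful way. In the simulations the error runs the other way: no setting showed inflation beyond Monte Carlo error, and clear conservatism appeared only with very strong factors. The second is that two unranked analyses leave room to pick the better result, including for the cost analyses, which depend on a significant primary outcome. The article labels neither analysis as primary, and the analysis plan it cites may settle the order, so this cannot be established from the article.

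What survives is narrow. The only test tied to the reported relative risk, risk difference, interval and p-value is unadjusted, and the logistic sentence as written does not supply those measures adjusted for the allocation factors.

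**Conclusion.** The point holds as a free improvement of low priority, not as a material error. The unadjusted comparison is valid and at most slightly conservative. Aligning it with the allocation would gain about 0.1 to 0.7 points of power with modest to strong factors, and up to about 1.7 with very strong ones, at quit rates that fit the planned sample size. These figures rest on assumed quit rates, factor odds ratios, prevalences and minimisation probability. The direction does not depend on those values, but the size does. No conclusion drawn from a positive chi-squared result would be unsafe on this account.

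**What to change.** State in the analysis section, or confirm in the analysis plan, that the main comparison of six-month abstinence is adjusted for sex, ethnicity (Māori, non-Māori) and FTND level (> 5, ≤ 5). Either a Mantel-Haenszel analysis over the 2 × 2 × 2 = 8 strata or logistic regression with marginal standardisation would serve. Report the adjusted risk difference and relative risk with 95% confidence intervals, and keep the chi-squared test as a supportive result.

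The cost is a sentence or two of wording, settled before the allocation code is broken. No new data are needed, since the three factors are recorded for everyone before randomisation, and the sample size need not change. If the analysis plan already says this, nothing further is required.

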#### Cost analyses

Costs analyses will be undertaken if a statistical difference between the groups is observed for the primary outcome of interest. Cost outcomes will include cost per quitter, cost per person reducing their daily cigarette consumption, and cost per quality adjusted life year of life saved among quitters (using discount rates of 0%, 5% and 10%). These data will then be compared with New Zealand data from Quitline and other NRT service providers, in addition to information from various international studies. This modelling will take a health sector perspective. However, the tobacco expenditure savings to individual smokers will also be calculated (for those who quit and cut down) to give a more societal perspective on the benefits (especially to low-income smokers). This calculation will use data on the daily amount smoked prior to quitting and the price of the particular products smoked. For those who cut down their consumption by a significant margin (i.e. 25% or more), the cost per person reducing their daily cigarette consumption will be calculated. Different approaches to assessing the benefit of years per life saved - including the use of New Zealand specific data on the relative risk of death as per Hunt et al 2005 [12], will also be explored.

#### Tolerability

All randomised participants who receive at least one dose of study treatment or control will be included in the planned analyses. Comparison of the frequency of treatment withdrawal between the treatment and the control group will be tested using Chi-square statistics. The numbers of participants discontinuing treatment prematurely for any reason will be summarised by treatment group and by reasons for discontinuation. Serious adverse events will be coded using ICD-10 AM codes. The incidence of all suspected serious adverse treatment reactions will be summarised by treatment group.

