**Discussion:**

Smoking prevalence in New Zealand has changed little in recent years (particularly in Māori, the indigenous people of New Zealand) and additional options for smokers who want to quit are needed. Although a variety of methods are available to help, many are expensive, have side effects, and despite their use most quit attempts still fail. This trial will test the balance of benefits and risks of a new strategy for people to overcome nicotine dependence. Since smoking is the leading cause of lost healthy life years in New Zealand, if proven effective this strategy is likely to have substantial public health benefits.

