**Figure 1 F1:**
[figure not shown]
**Schematic of treatment allocation during intervention period**.

• Control group: Participants allocated to the control arm of the trial will be asked to stop smoking completely on their chosen Quit day and will be supported by Quitline in the usual way for eight weeks, with counselling/advice and NRT in the form of a patch, gum and/or lozenge (Figure 1).

Current standard cessation practice at the New Zealand Quitline (as at December 2010) is as follows (other cessation providers in New Zealand do not follow the process outlined here): Quitline issues by post, a Quit Card (with a 90 day expiry) for eight weeks supply of up to three NRT products (patch, gum and/or lozenge) and makes routine support calls by telephone over eight weeks. These support calls are administered by the Quitline advisors as required. Quitting support generally involves an average of three follow-up telephone calls, each lasting about 10-15 minutes. However, if people do not wish to receive support calls, they are not scheduled but callers are advised that they can phone Quitline at any time for support. Participants are advised to take the Quit Card to a pharmacist in exchange for subsidised patches, gum and/or lozenges (NZ$3 per item per four-week course of NRT). The strength of NRT patch, gum, and/or lozenges to be used by each participant is determined by the Quitline advisor (as per their dosage guidelines) as to the degree of each person's nicotine dependency. "Quit day" in this study will refer to the day each participant stops smoking cigarettes containing nicotine.

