#### Secondary outcomes

The following secondary outcome measures will be assessed at three and six weeks after the Quit date in the treatment group only:

• Information related to the use of the nicotine-free cigarettes: Participants will be asked for their views on the use of the nicotine-free cigarettes (including concerns, whether they liked the taste of them, etc), and whether the six weeks use of the cigarettes was adequate. The number of nicotine-free cigarettes and normal cigarettes smoked each week during the intervention period will also be recorded.

• Information related to the use of the NRT: Participants will be asked about their use of NRT during the treatment period.

The following secondary outcome measures will be assessed in all participants at three weeks, six weeks, three months and/or six months after the Quit date:

• The physical signs and symptoms associated with withdrawal at three and six weeks: Measured using the Mood and Physical Symptoms Scale (MPSS) [7]. Additional withdrawal questions will also be asked related to the frequency of disturbed sleep, anxiety, mouth ulcers, cough, impatience, dizziness and increased dreaming [8].

• Self-rated chances of quitting at three and six weeks: Measured on a scale of one to five, where one is very low and five is very high.

• Proportion of participants who have stopped smoking at three weeks, six weeks and three months: Defined as no nicotine cigarettes (not even a puff) in the past seven days.

• Continuous abstinence: Defined as self-report of smoking no more than five nicotine cigarettes from the Quit date, collected at all time points.

• Proportion of participants who have significantly reduced daily smoking level at six months: Defined as reducing consumption by at least 25% (in terms of numbers of cigarettes per day or weight of loose tobacco per day).

• Number of cigarettes currently smoked per day: If the participant is still smoking (all times points). Pack size (and how long pack lasts) if smoking roll-your-owns.

• Cost information: Cost outcomes will include cost per quitter, cost per person reducing their daily cigarette consumption, and cost per Quality Adjusted Life Year of life saved among quitters. The tobacco expenditure savings to individual smokers will also be calculated using data on the daily amount smoked prior to quitting and the price of the particular products smoked.

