• Use of NRT: Participants will be asked about continued use of any NRT (including type, dosage, flavour, and frequency of use) at all time points.

• Use of non-NRT methods of cessation at six months: Participants will be asked about their use of non-NRT methods of cessation such as buproprion, clonidine, nortriptyline, varenicline, acupuncture etc.

• Alcohol use and abuse at six months: Measured using the AUDIT-C [9].

• Serious adverse events: Information regarding any serious adverse events and whether they are related to treatment will be collected at all time points.

• Concomitant medication: collected at all time points

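### The only adverse-event incidence stated by arm is limited to suspected serious reactions in dosed participants, which does not match the declared outcome of any serious adverse event in all participants

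*Protocol article*

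**What the plan says.** Three statements in the Tolerability section of the protocol article fix the safety analysis.

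- Population: "All randomised participants who receive at least one dose of study treatment or control will be included in the planned analyses".
- Serious adverse events as a whole: "Serious adverse events will be coded using ICD-10 AM codes". No summary by arm is stated for them.
- The by-arm incidence: "The incidence of all suspected serious adverse treatment reactions will be summarised by treatment group".

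The section also makes by-arm comparisons that do not depend on relatedness: "Comparison of the frequency of treatment withdrawal between the treatment and the control group will be tested using Chi-square statistics". Premature discontinuations are to be listed by group and reason.

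The Secondary outcomes section describes the outcome differently. Its list opens with "The following secondary outcome measures will be assessed in all participants", and the entry for serious adverse events reads: "Information regarding any serious adverse events and whether they are related to treatment will be collected at all time points". Relatedness is an additional item recorded for each event; it does not decide which events count.

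On supply, Study intervention has the cigarettes couriered to the treatment arm. For NRT, used in both arms and the only product in the control arm, "Participants are advised to take the Quit Card to a pharmacist in exchange for subsidised patches", with a part-charge of NZ$3 per item per four-week course.

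**The concern.** The declared outcome and the stated analysis differ in both the events counted and the people counted. Each difference replaces something fixed by randomisation with something determined afterwards.

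**Events.** Whether an event is a suspected reaction is a judgement. Blinding leaves participants, the Quitline staff who make the follow-up calls, and the project co-ordinator aware of allocation. Under Withdrawal criteria, the co-ordinator also receives reports of deaths and serious events within 30 days of discontinuation. Both arms get NRT and support, but only one gets an unfamiliar smoked product that could be blamed. The article does not say who judges relatedness or whether that person is blinded, so attribution could differ by arm.

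**People.** The term dose is not defined for either arm. A treatment participant who never collects NRT could still enter the dosed set through a couriered cigarette. A control participant who never redeems the Quit Card might have no dose at all.

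At stake is the safety side of the conclusion. The abstract says: "This trial will test the balance of benefits and risks of a new strategy". No interim analysis is planned and there is no data monitoring committee, so the final by-arm table is the main comparative look at harm. Withdrawal and discontinuation do not replace it: study treatment ends at six to eight weeks, while serious events are collected to six months.

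**Working it through.** The article states no safety figure, so there is none to reproduce. The only design figures used are 705 per arm and 20% loss to follow-up (Sample size). All rates below are assumptions.

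**1. The two sections side by side**

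| | Secondary outcomes | Tolerability |
|---|---|---|
| Events | any serious adverse event, with relatedness recorded | suspected serious treatment reactions |
| People | all participants | randomised and dosed |
| All serious events | collected at every time point | coded; no by-arm summary stated |

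Under Withdrawal criteria, data collection continues after treatment stops. The data for the wider outcome are therefore meant to exist.

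**2. Effect of the attribution filter**

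Let n = 705 per arm, r = true risk of a serious event (equal in both arms), and a1 and a0 = shares judged related in the treatment and control arms. Expected suspected reactions are n × r × a1 and n × r × a0, so the apparent ratio is a1/a0 whatever r is.

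With r = 4%, all events are 705 × 0.04 = 28.2 per arm, a true ratio of 1.0.

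| a1 v a0 | Suspected reactions | Apparent ratio |
|---|---|---|
| 30% v 30% | 8.5 v 8.5 | 1.0 |
| 40% v 20% | 11.3 v 5.6 | 2.0 |
| 50% v 10% | 14.1 v 2.8 | 5.0 |

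For r from 2% to 6%, all events run from 14.1 to 42.3 per arm. The 40% v 20% row then runs from 5.6 v 2.8 to 16.9 v 8.5, with the ratio still 2.0. Reversing the shares reverses the ratio, so the article does not determine a direction.

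**3. What an all-event table would give**

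The 95% half-width of the risk difference is 1.96 × sqrt(2r(1 − r)/n).

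- r = 4%, n = 705: 1.96 × sqrt(2 × 0.04 × 0.96/705) = 0.0205, about ±2.0 points.
- r = 2%: 1.96 × sqrt(2 × 0.02 × 0.98/705) = 0.0146, about ±1.5 points.
- r = 6%: 1.96 × sqrt(2 × 0.06 × 0.94/705) = 0.0248, about ±2.5 points.
- r = 4% with 20% lost (705 × 0.80 = 564): 1.96 × sqrt(2 × 0.04 × 0.96/564) = 0.0229, about ±2.3 points.

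If 10% of events were judged related in both arms, 0.10 × 28.2 = 2.8 per arm would remain. That shows sparse counts, not bias.

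**4. Effect of the dosed set**

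Number included = 705 × uptake of a first dose.

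| Uptake, treatment v control | Included | Dropped |
|---|---|---|
| 95% v 95% | 670 v 670 | 35 v 35 |
| 95% v 85% | 670 v 599 | 35 v 106 |
| 95% v 70% | 670 v 493 | 35 v 212 |

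Unequal denominators alone do not distort an incidence. If those dropped carry the same 4% risk, the middle row gives 26.8/670 and 24.0/599, both 4.0%. Bias arises only if those dropped differ in risk from those kept and the selection differs by arm. The dosed set removes the protection of randomisation against this, but the article does not show that it happens.

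**The case against.** The strongest reply is that silence is not exclusion. The article nowhere says that other serious events will not be tabulated by arm; it refers to a pre-specified statistical analysis plan that is not shown, and such a plan commonly adds tables. This stands as a limit: the plan may already contain an all-event table. It does not remove the point, because the article goes beyond silence. It names a by-arm quantity and a population, and neither matches its own outcome list.

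Other objections narrow the point:

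- A reader might infer that the trial is open-label and that unblinded staff decide relatedness. The documents do not support this. The trial is single-blind, with the committees and most trials-unit staff blinded, and the assessor is unnamed and could be one of them.
- A reader might infer that controls who do not redeem the Quit Card drop out of the analysis. Usual care is defined as NRT plus behavioural support, and dose of control is undefined, so this is only a possibility. Nor is being sent cigarettes the same as smoking one: treatment participants are told to try other techniques first.
- A dosed population is conventional for tolerability, and withdrawals and discontinuations are also compared by arm. Both are true. Neither supplies the incidence of serious events by randomised group.
- The formal objectives include no comparative safety test; the wording about benefits and risks comes from the abstract and the Discussion. This limits the consequence but leaves serious events as a listed secondary outcome.

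**Conclusion.** The mismatch is established from the text: the outcome is any serious adverse event in all participants, while the stated by-arm incidence covers suspected serious reactions in a dosed set. Followed literally, the Tolerability section gives a comparison of harm conditioned on causality judgement and on dosing, not a randomised one.

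Differential attribution and differential entry to the dosed set are risks that the design leaves open; neither is shown to occur. Their size cannot be obtained from the article. The apparent ratios of 2.0 and 5.0 rest wholly on assumed attribution shares, and the numbers dropped rest on assumed uptake.

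A reader might go further and conclude that the planned table could show neither harm nor its absence. That is too strong. Much of the imprecision comes from rare events, and an all-event comparison with a half-width of about 2 points on an assumed 4% risk could not establish absence of harm either. What that comparison would remove is dependence on attribution and on a first dose. Loss to follow-up would still leave some data missing.

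The primary outcome, sample size and data collection are unaffected. The analysis text can be corrected at any time before unblinding.

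**What to change.** In Tolerability, make the main safety summary all serious adverse events, regardless of relatedness, by randomised arm in all randomised participants (1,410), with the risk difference and 95% confidence interval. Show suspected reactions as a subset of that table, and keep the dosed set as a supportive analysis. Add one sentence defining dose for each arm, and one saying who judges relatedness and whether that person is blinded. If the statistical analysis plan already specifies the all-event table, aligning the article's wording with it is enough.

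The cost is one additional table and two sentences. The events are already to be collected from all participants, with relatedness, and coded.
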